## Abstract

**Background:**

Inadequacy in mental health care in low and middle income countries has been an important contributor to the rising global burden of disease. The treatment gap is salient in resource-poor settings, especially when providing care for conflict-affected forced migrant populations. Primary care is often the only available service option for the majority of forced migrants, and integration of mental health into primary care is a difficult task. The proposed pilot study aims to explore the feasibility of integrating mental health care into primary care by providing training to primary care practitioners serving displaced populations, in order to improve identification, treatment, and referral of patients with common mental disorders via the World Health Organization Mental Health Gap Action Programme (mhGAP).

**Methods/Design:**

This pilot randomized controlled trial will recruit 86 primary care practitioners (PCP) serving in the Puttalam and Mannar districts of Sri Lanka (with displaced and returning conflict-affected populations). The intervention arm will receive a structured training program based on the mhGAP intervention guide. Primary outcomes will be rates of correct identification, adequate management based on set criteria, and correct referrals of common mental disorders. A qualitative study exploring the attitudes, views, and perspectives of PCP on integrating mental health and primary care will be nested within the pilot study. An economic evaluation will be carried out by gathering service utilization information.

**Discussion:**

In post-conflict Sri Lanka, an important need exists to provide adequate mental health care to conflict-affected internally displaced persons who are returning to their areas of origin after prolonged displacement. The proposed study will act as a local demonstration project, exploring the feasibility of formulating a larger-scale intervention study in the future, and is envisaged to provide information on engaging PCP, and data on training and evaluation including economic costs, patient recruitment, and acceptance and follow-up rates. The study should provide important information on the WHO mhGAP intervention guide to add to the growing evidence base of its implementation.

**Trial registration:**

SLCTR/2013/025.

## Background

Inadequacy in mental health care in low and middle income countries (LMIC) has been an important contributor to the rising global burden of disease [1]. The treatment gap in mental health in LMIC has been well researched, and a strong evidence base is rapidly building through numerous epidemiological and interventional studies in resource-poor settings [2,3]. The importance of incorporating mental health care into existing primary care systems in LMIC has been recognized as a priority by global health policymakers such as the World Health Organization (WHO), global leaders in mental health research, and national governments of LMIC [4-6]. Scaling up of primary care services and task-shifting approaches have been recognized as key concepts in integrating mental health with primary care provision in resource-poor settings [7,8].

Common mental disorders (CMD) are a broad spectrum of conditions, which include depressive and anxiety disorders [9]. They are predominantly present in primary care settings, especially in LMIC [10,11]. However, low detection or non-detection by primary health care providers, increased rates of symptomatic treatment, low referral rates for specialist care, and increased healthcare costs are all associated with CMD in primary care settings in LMIC [10,12]. Lack of adequate training for primary care physicians, lack of adequate human resources (number of physicians), inadequate health systems, and lack of adequate policy attention are seen as the main barriers to effective treatment of CMD through integrating mental health into primary care in LMIC [10,11,13].

In conflict-affected situations, existing resource-limited health systems can be severely affected, limiting any provision of care to populations; this is especially salient for forced migrants in LMIC [14]. Mental health care may be considered a secondary consideration in post-conflict settings, where primary care resources are usually allocated for more immediate health concerns [15,16]. However, there is strong evidence that conflict-driven forced migrants have increased rates of mental disorders including CMD and post-traumatic stress disorder [17,18]. Primary care, however limited, is often the only available service option for the majority of forced migrants, except for those refugees who manage to migrate to more resourceful countries or regions. Integration of mental health into primary care for conflict-affected forced migrants is adifficult task given the political, cultural, economic, and security complications involved. However, there is some evidence that such integration is feasible even in difficult settings, with the potential to improve mental health of affected populations [19].

Although it is recognized that Sri Lanka has a very effective primary care system, the primary care treatment gap for mental health is extensive [20]. Owing to the recently concluded three-decade conflict, the country has several resource-poor regions where there are forced internal migrants, with some having lived in prolonged displacement for over 20 years, and return migration having only recently started. Populations of internally displaced persons (IDP) who experienced prolonged forced migration in Sri Lanka have shown increased rates of CMD (18.8%) compared with national figures, especially of somatoform disorders (14% compared with a national prevalence of 4.2%) and major depression (5.1% compared with a national prevalence of 2.6%), and they lack adequate services of specialist mental health care providers, including psychiatrists [18,20,21]. This is evident among the northern Muslim IDP, displaced as a result of conflict in 1990 in the northern province (mainly Mannar district), who have been living in displacement in the Puttalam district of the north-western province, and are currently returning to areas of origin [18]. Return migration areas in the Mannar district in particular lack adequate healthcare facilities to cater for the influx of returnee populations. For those IDP opting to live in Puttalam, available mental health services are also limited, and the Puttalam district did not have the services of a psychiatrist until 2008. Although the Ministry of Health has taken steps to train a new category of Medical Officers of Mental Health (MOMH) to provide increased mental health care in the absence of specialist psychiatrists, their services are also insufficient to match the existing healthcare needs. Primary care physicians, such as general practitioners, medical officers in government primary care facilities, and medical officers in tertiary care outpatient departments located in the Puttalam or Mannar districts are the front line and often the only available option for mental health care of IDP. However, these physicians do not have the adequate training or skills to identify and treat mental disorders in the busy primary care setting in which they work.

Against this background, the proposed pilot study titled "An intervention to improve mental health care for conflict-affected forced migrants in low-resource primary care settings: a WHO MhGAP-based pilot study in Sri Lanka (COM-GAP)" aims to integrate mental health care into primary care by providing training to primary care practitioners (PCP) serving populations of IDP to improve identification, treatment, and referral of patients with CMD via the WHO Mental Health Gap Action Programme (mhGAP). The mhGAP initiative, introduced in 2008 by the WHO, incorporates evidence-based guidelines on managing mental, neurological, and substance abuse disorders in the primary care setting by non-specialist healthcare workers [7,22]. The mhGAP Intervention Guide (mhGAP IG), introduced in 2010, is a valuable manual that can be used as a resource in training non-specialists in primary mental health care, and is currently in its evaluation and implementation stage in several countries [7,8].

The primary objective of the proposed study is to assess the feasibility of improving/increasing identification, treatment, and referral of CMD by PCP working with a group of displaced and returning forced migrants in a resource-poor, rural, primary care setting via a training program based on the WHO mhGAP IG. This will be carried out by developing a pilot randomized controlled trial (ACT) in the north and north-western provinces of Sri Lanka. The main hypothesis of the study is that training intervention using mhGAP IG will increase rates of correct identification, treatment, and specialist referral rates of the PCP. It is envisaged that training PCP to efficiently identify, treat, and refer patients with CMD will reduce the acute and long-term disease burden, reduce service-provision costs, and provide effective/accessible mental health care to vulnerable/traumatized IDP. As South Asia faces continuous problems relating to mass forced migration, this study may provide important evidence on reducing the treatment gap for vulnerable populations in the region, with a high potential for scaling up in other resource-poor settings. This is the first study of its kind to be undertaken in Sri Lanka, and is planned as a local demonstration study to aid a future larger-scale intervention.

## Methods/design

### Study design and setting

The study will be carried out in primary care settings (outpatient departments of government hospitals, government rural hospitals, government central dispensaries, and private medical clinics) in the Puttalam and Mannar districts of the north and north-western provinces of Sri Lanka, where conflict-affected, long-term displaced/returning migrants are located. It will be conducted as a feasibility study in the form of a pilot RCT.

### Participants

Two groups of participants will be recruited. The main participant group will be PCP working in government health services or private practices in the primary care institutions listed above within the geographical areas of the Puttalam and Mannar districts. The secondary participant group will be patients diagnosed with CMD (depression, anxiety, somatoform disorder/medically unexplained symptoms, or suicidal ideation) by the recruited PCP during the study period. PCP will be approached at the primary care institutions (government and/or private) by the principal investigator (PI) and the research team. They will also be approached (as applicable) through the Sri Lanka College of General Practitioners and other relevant organizations. Appropriate permission has been sought and obtained from the Ministry of Health and Provincial Ministries of Health.

### Inclusion and exclusion criteria

To be included, PCP will need to: have 5 or more years of experience, have full registration with the Sri Lankan Medical Council, and be providing a minimum of 4 hours/day of primary care to IDP populations. PCP will be excluded if: they are psychiatrists, have secondary mental health training, less than 5 years of service, and work less than 4 hours/day with IDP populations.

To be included, patients will need to: belong to a specific IDP groups, and be adult (18 years or older). Patients aged under 18 years will be excluded, as the intervention training focuses on adult population. Patients diagnosed with serious mental disorders will also be excluded as the intervention training focus is on CMD.

### Sampling

It must be highlighted that this is purely a feasibility study. Therefore, as a pilot RCT, 43 PCP for each arm (total of 86) are estimated to be a sufficient sample size, including drop-out allowance [23,24]. Specific global evidence required for sample size calculation through standard methods is not available. Sample size calculations for patients are not required, as they will not be included in the trial, and no outcomes will be measured for this group (more details explained in the next section).

### Intervention

The training intervention will be based on the mhGAP IG developed by the WHO. Only relevant modules (depression, medically unexplained symptoms, alcohol abuse, and suicide) will be used for the training. The training will be based on a complete training guide and material provided by the WHO, which contains the necessary course material for trainees and preparatory and guidance materials for trainers. It will be conducted by the PI (who has been trained by the Royal College of Psychiatrists affiliated mhGAP training programme, UK), mhGAP IG experts, and another clinically experienced psychiatrist. Training programs will be conducted as a full-day course for five consecutive days, as originally designed by the WHO. The training intervention will be given to 43 (approximately half) of the recruited PCP in the intervention arm, randomized by appropriate techniques. Participants in the control arm will be given a similar training in mhGAP after the completion of the study.

Training will take place after an initial 3 month monitoring period of the whole sample from the date of recruitment (90 day monitoring period for each participant from the date of recruitment). During this period, all PCP are required to inform the study coordinator immediately on diagnosing a primary care patient with CMD. The PCP is required to obtain written informed consent from each patient if they agree to be contacted by the research team, prior to informing the coordinator. All PCP will be given initial training on ethics and informed consent procedures prior to commencing the study.

After the 5 day training period of the intervention group, both arms will be monitored again for a 3 month period. Those in the intervention arm will be required to use the mhGAP guide to diagnose, treat, and refer patients with possible mental health problems whom they encounter in their respective primary care settings. The control arm will be requested to continue their existing diagnostic and treatment practices. Participants in both arms will be required to communicate any CMD diagnoses to the study coordinator immediately.

During the first and second 3-month monitoring periods, the study coordinator will gather a list of patients diagnosed by the participant PCP (from both intervention and control arms) on a daily and weekly basis. These patients will then be approached individually by the study coordinator, who will explain the purpose of the study. The coordinator will provide an information leaflet and obtain secondary written consent from each patient. Consenting patients will then be directed to the study psychiatrist, who will reassess them according to mhGAP-based criteria for concurrence with the initial PCP diagnosis. Unless absolutely necessary, the psychiatrist will not modify or change the treatment or management outlined by the PCP. For those patients categorized as referrals to specialist care, their treatment and management will be provided by the study psychiatrist. However, referral patients will be completely free to decide if they want to be treated by the study psychiatrist or to seek care from other government or private specialist psychiatrists. All patients consenting to be involved in the study will be compensated for travelling costs or provided with travel if they prefer. No other compensation will be offered. For COM-GAP study phases according to CONSORT guidelines, please see the Additional file 1.

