### Primary outcomes and statistical analysis

Referral rates before and after the intervention will be measured for all PCP. Rates of study psychiatrist-verified diagnoses will be measured. Quality of adherence to mhGAP guidelines for treatment and management will be assessed for the intervention arm. Knowledge levels at the three test points will be measured for all PCP. For PCP in the intervention arm, knowledge levels will be assessed during each day of the training program. Overall comparisons will be made between the intervention and control arm rates for referral, correct diagnosis, and knowledge increase. Secondary outcomes include concurrence between the clinical diagnosis and the screening instrument and basic economic evaluation (described later).

No interim analysis will be carried out, and analysis will commence only at the end of the full study period. Because this is a pilot study, the analysis will be focused on primary feasibility, and therefore will primarily be descriptive in nature, with estimations of confidence intervals as appropriate [24]. As power calculations will not be carried out, it would not be appropriate to conduct analyses aimed at testing hypotheses [24]. The main analysis will be based on difference in outcomes of intervention and control arms using two-way analysis of variance (ANOVA). Appropriate consideration will be given to potential confounders. Results will be used to formulate sample size calculation for a larger intervention.

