### Ethical issues

Ethics approval has been obtained from the Ethics Review Committee, Faculty of Medical Sciences, University of Sri Jayewardenepura, Sri Lanka. Informed written consent will be obtained from eligible PCP after the initial approach, and an information leaflet will be provided to them. An appropriate length of time (minimum 1 day) will be allowed for decision-making. If the PCP is interested, the study coordinator will obtain their written consent. Each patient diagnosed by individual PCP during study period will be asked twice for consent. In first instance, the PCP will explain the study and obtain consent from the patient for the study team to approach the patient. The patient will be told that the treatment will strictly not depend on their decision to participate. PCP will be trained in ethical aspects of informed consent, and will be strongly encouraged to prevent undue inducement or coercion. However, given the doctor-patient relationship in Sri Lanka, this is extremely difficult to prevent. The study team will make regular spot-checks with PCP to ensure that systematic coercion is not present. If a patient consents to be approached by the study team, then the study coordinator will approach the patient and re-explain the study with an information leaflet. Again, after an appropriate time gap, the patient will be asked to decide to participate. If they consent, the study coordinator will make subsequent arrangements for the patient to have a clinical interview with the study psychiatrist. From the moment of recruitment, all patients will be anonymized to the study team, and data will be entered using a numbered coding system. Both PCP and patients will be explicitly informed of the feasibility nature of the pilot study during the recruitment process. Both PCP and patients will be able to withdraw at any time during the study without presenting a reason. Maximum efforts will be made to ensure data protection and confidentiality. If the study psychiatrist discovers significant medical errors in the treatment and management by PCP, they will be individually approached and advised to rectify the errors. As mentioned above, referral patients have the choice to refuse the services of the study psychiatrist and seek specialist care elsewhere. If any serious mental disorders are diagnosed by the PCP during the study period, those patients will be advised to seek immediate specialist advice and refer to specialist care. The study team will provide full support in such situations, both to the PCP and the patient, as required. Information leaflets and consent forms for PCP will be in English, and for patients they will also be available in Sinhala and Tamil.

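### The plan does not settle whether a CMD diagnosis is reported when the patient declines contact; if consent must come first, overall patient acceptance cannot be computed and list-based counts depend on consent success

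*Protocol article*

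**What the plan says.** All of this is in the protocol article.

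- **Intervention, baseline monitoring:** "all PCP are required to inform the study coordinator immediately on diagnosing a primary care patient with CMD". The consent rule follows directly: the PCP must "obtain written informed consent from each patient if they agree to be contacted by the research team, prior to informing the coordinator".
- **Intervention, after training:** "Participants in both arms will be required to communicate any CMD diagnoses to the study coordinator immediately". This sentence carries no consent condition.
- **Intervention, both periods:** "the study coordinator will gather a list of patients diagnosed by the participant PCP". The coordinator then approaches these patients one by one, and is to "obtain secondary written consent from each patient".
- **Ethical issues:** at the first of the two consent steps, "the PCP will explain the study and obtain consent from the patient for the study team to approach the patient". The coordinator's approach is made conditional on that consent.
- **Abstract (Discussion):** the pilot is expected to yield "data on training and evaluation including economic costs, patient recruitment, and acceptance and follow-up rates". The main Discussion repeats this for patient recruitment, acceptance and follow-up.
- **Primary outcomes and statistical analysis:** "Referral rates before and after the intervention will be measured for all PCP", and the arms are compared on referral and correct diagnosis. No data source or denominator for the referral rate is given.

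**The concern.** A PCP whose patient declines contact has two instructions that cannot both be followed as written: report the diagnosis at once, and report only after written consent. No anonymous report is described that would satisfy both. PCPs may resolve this differently, so the counts may not mean the same thing from one PCP to the next.

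Two products of the pilot are exposed. The first is patient acceptance, which a feasibility study needs in order to plan recruitment for the larger trial. The second is any count built from the coordinator's list. Such a count would combine how often a PCP diagnoses or refers with how often that PCP's patients agree to be contacted. The PCP obtains that agreement personally and knows whether he or she has been trained.

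**Working it through.** The article gives no consent or acceptance figure, so there is none to reproduce. The check sets the passages side by side and then does arithmetic on assumed consent rates.

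**1. Who is on the coordinator's list?**
- Under Intervention, the coordinator goes on to approach the patients on the list individually.
- Under Ethical issues, a patient is approached only after agreeing to it with the PCP.
- Together these imply that the list holds first-stage consenters only.
- Measurements describes no PCP log, tally or record review that would capture the others.
- Against this stand the two Intervention sentences requiring immediate reporting, the second covering any CMD diagnosis. The text is therefore in conflict, and the operational passages lean towards consent first.

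**2. Acceptance if consent comes first.** Let s1 be the proportion agreeing with the PCP and s2 the proportion of those agreeing with the coordinator. Overall acceptance = s1 × s2, and only s2 is observed. Assume s2 = 80%.

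| s1 (assumed) | Overall acceptance | Study would show |
|---|---|---|
| 50% | 0.50 × 0.80 = 40% | 80% |
| 70% | 0.70 × 0.80 = 56% | 80% |
| 90% | 0.90 × 0.80 = 72% | 80% |

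**3. Counts by arm.** With c the first-stage consent rate, apparent count ratio = true ratio × (c intervention / c control). Take a true ratio of 1, with 10 referrals per PCP in each arm.

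| Control (assumed) | Intervention (assumed) | Counts | Apparent ratio |
|---|---|---|---|
| 70% | 70% | 7.0 v 7.0 | 1.00 |
| 70% | 85% | 7.0 v 8.5 | 1.21 |
| 85% | 70% | 8.5 v 7.0 | 0.82 |

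With equal consent the ratio is right, but both counts are 30% too low.

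**4. Referrals per reported patient.** Suppose 20 CMD diagnoses per PCP, 10 of them referred, and consent unrelated to referral. At 70% and 85% consent the rates are 7/14 and 8.5/17, both 50%, so the ratio is 1.00. This form of the rate is distorted only if consent also depends on referral status, to a degree that differs by arm.

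**5. Use of the baseline period.** If consent is 70% in one arm and 85% in the other in both periods, the count ratio is 1.21 before and 1.21 after, and 1.21/1.21 = 1.00. Only a change in consent after training that differs by arm would bias a before-and-after comparison.

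**The case against.** The strongest reply is that nothing bars a PCP from reporting a refuser. The consent sentence can be read as applying only where the patient agrees to contact, with every diagnosis notified regardless. That reading is open. A reader might infer that refusers leave no trace and that acceptance has no valid denominator at all, but the article does not go so far: any CMD diagnosis is to be communicated, and second-stage acceptance keeps its denominator, the patients whom the coordinator approaches. What remains is that the article does not choose between the readings, and the list procedure fits the narrower one better.

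A reader might also infer that the referral comparison is biased in favour of training. The documents do not support that. The source of the referral rates is not stated, so their dependence on the list is an inference. A difference in consent between arms is assumed, not shown, and could run either way. A rate per reported patient may largely cancel it. All PCPs receive the same ethics and consent training, there is a baseline period, and the analysis is primarily descriptive.

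Nor is there support for supposing that the first-stage loss is the larger one. Ethical issues concedes that undue influence by the doctor is hard to prevent, which could make refusal to the PCP the rarer of the two. With 5% first-stage refusal (assumed), overall acceptance would be 0.95 × 0.80 = 76% against 80% shown, a small gap.

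Forms and logs may also be set out in a full protocol that is not shown. That answers a complaint about a missing form, but not two printed instructions that disagree.

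**Conclusion.** The concern holds as an unreconciled conflict over reporting, with consequences that depend on which rule PCPs follow. If consent comes first, overall patient acceptance cannot be recovered. The one observable rate would be the same 80% for overall acceptance anywhere from 40% to 72%, under the assumed stage rates. Diagnosis counts from the list would depend on consent success, and so would referral counts if they come from the list. Psychiatrist-verified diagnoses depend on both consents under either reading.

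Between-arm bias is a possibility and not a finding. It needs consent to differ by arm after training, and its size and direction are unknown. The 1.21 and 0.82 are illustrations on counts, not estimates. The change is worth making because it is inexpensive and supplies a denominator that the pilot needs. Trial status says that the study has commenced, so refusers not counted now may not be recoverable later.

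**What to change.** Reconcile the reporting sentences in Intervention with the list procedure there and with the consent steps in Ethical issues, so that one rule covers patients who decline contact:

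- The PCP reports every CMD diagnosis as a non-identifiable tally line: date, diagnosis group, referred yes/no, agreed to contact yes/no. Identifying details go to the coordinator only after written consent.
- Crude diagnosis and referral rates are computed from the full tally, with the denominator stated.
- Acceptance is reported at each consent stage, by arm and by monitoring period.
- Psychiatrist-verified diagnoses, and the correctness of referrals that the Abstract lists among the primary outcomes, are reported as limited to consenting patients. A tally cannot supply these for refusers.

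The cost is slight extra recording time for PCPs and an ethics notification or amendment for the anonymous counts. If PCPs have already been following different rules, the date of the change should be recorded and counts before and after it kept apart.

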### Allocation concealment

It will not be possible to mask the study team to the status of the PCP, as they will be aware of the PCP participants in the training intervention arm. The study psychiatrist will be blinded/masked to the randomization status of the PCP, and therefore be unbiased with regard to the patients originating from each PCP (that is, whether a patient was diagnosed by a trained or untrained PCP). The study psychiatrist will therefore not be involved in the training program. In addition, patients will also be blinded to the PCP randomization status.

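### The psychiatrist's reference diagnosis is not protected from the PCP's own diagnosis: masking covers trial arm only, so the verified-diagnosis rate is open to anchoring and should be labelled mhGAP concordance

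*Protocol article*

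**What the plan says.** Under Intervention, the coordinator lists the patients diagnosed by PCPs in both arms, in both monitoring periods. Those who consent are sent to the study psychiatrist, "who will reassess them according to mhGAP-based criteria for concurrence with the initial PCP diagnosis". Save in exceptional need, "the psychiatrist will not modify or change the treatment or management outlined by the PCP". Ethical issues adds a route for action: "If the study psychiatrist discovers significant medical errors in the treatment and management by PCP", the PCP is approached and advised.

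The same Intervention section sets what each arm does after training. "Those in the intervention arm will be required to use the mhGAP guide to diagnose, treat, and refer patients". By contrast, "The control arm will be requested to continue their existing diagnostic and treatment practices", and control PCPs are trained only once the study is over.

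Allocation concealment masks the psychiatrist to the PCP's randomized arm and keeps the psychiatrist out of the training. From this it concludes that the psychiatrist will "be unbiased with regard to the patients originating from each PCP". The section Primary outcomes and statistical analysis lists the rate of psychiatrist-verified diagnoses, compares correct diagnosis between arms, and uses the results to size a larger trial. Concurrence with the screening questionnaire (PHQ) is a secondary outcome.

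**The concern.** A reference diagnosis is useful to the extent that it is made without sight of the diagnosis it is meant to check. Here the psychiatrist's task is framed as checking agreement, and the only masking described concerns trial arm. Someone who does not know the arm can still be drawn towards the diagnosis already made, and masking to arm does nothing about that.

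The second issue is the yardstick. One arm is trained in, and required to use, the guide from which the psychiatrist's criteria come. The other arm is not. Better agreement in the trained arm could partly reflect a shared criterion.

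Three uses of the rate are affected: the between-arm comparison of correct diagnosis, the sizing of the larger trial, and the economic evaluation, which ties cost to the primary outcome to obtain a cost per extra patient detected.

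**Working it through.** The article gives no diagnosis rates, effect size or power calculation, so there is no planned figure to reproduce on this point. The check is of the text first, then of direction on assumed values.

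**What the psychiatrist can be taken to know**
- Every patient sent has already been diagnosed by a PCP (Intervention), so PCP-positive status is known by design.
- The task is defined as concurrence with the PCP's diagnosis (Intervention).
- Leaving the PCP's management unchanged, and finding errors in it, both require seeing it at some point (Intervention; Ethical issues).
- Masking is stated for arm only (Allocation concealment). The anonymization in Ethical issues concerns patient identity, not the diagnosis.

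That the PCP's diagnosis is seen before the reference diagnosis is made is thus a strong inference, not a stated fact. What is certain is that nothing in the text prevents it.

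**Anchoring.** Let p be the true share of PCP diagnoses that are correct, and a the share of wrong diagnoses that the psychiatrist confirms because the PCP's diagnosis is known. Since the psychiatrist is masked to arm, take a as equal in both arms.

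Verified rate = p + (1 − p)a, so the arm difference = (pI − pC)(1 − a).

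Assume pC = 50% and pI = 70%, a true difference of 20 points:

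| a | Control | Intervention | Difference |
|---|---|---|---|
| 0 | 50% | 70% | 20 points |
| 0.25 | 0.50 + 0.50 × 0.25 = 62.5% | 0.70 + 0.30 × 0.25 = 77.5% | 15 points |
| 0.50 | 0.50 + 0.50 × 0.50 = 75% | 0.70 + 0.30 × 0.50 = 85% | 10 points |

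Both rates rise and the difference shrinks. With no true difference (50% in both arms, a = 0.25) both read 62.5%, so anchoring of this kind does not create a difference.

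**Shared yardstick.** Let d be the share of patients in whom mhGAP-based criteria and an independent standard would disagree. Let gI and gC be the probabilities that trained and control PCPs side with mhGAP in those patients. The spurious difference is s = d(gI − gC). It is in favour of the trained arm if training moves PCPs towards mhGAP, and it arises only in the second monitoring period, because neither arm is trained in the first. A before-after comparison therefore does not remove it.

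**Net direction.** Taking the two as additive before anchoring acts, the observed difference is (1 − a)(Δ + s), where Δ is the true difference. It equals Δ when s = Δa/(1 − a). With Δ = 20 points and a = 0.25 that is 20 × 0.25/0.75 = 6.7 points. Over a wide assumed range, s runs from 0.05 × (0.75 − 0.50) = 1.25 points to 0.20 × (1 − 0) = 20 points, on both sides of 6.7. These values only show that the sign of the net bias is open. They are not estimates for this trial.

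**The case against.** The article states the purpose of the reassessment, not the order of forms or who scores agreement. A full protocol may settle that, and the management could be shown only after the diagnosis is recorded. This stands as a limit on the point: a reader might infer that the psychiatrist certainly has the PCP's diagnosis in hand, and the text does not say so. It does not dispose of the point, because the article defines the task as concurrence, describes the masking, and confines that masking to arm.

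The claim of no bias under Allocation concealment, read with its own parenthesis, is about whether the PCP was trained. On that reading it does not assert an independent reference standard. That is fair, and it is why the remedy is to word the claim as masking to allocation.

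mhGAP criteria are a defensible target for a trial of mhGAP training, applied alike to both arms and both periods. That stands. A reader might infer that a non-mhGAP classification must become the primary yardstick. This would change what the trial measures, and the documents do not require it.

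A reader might also infer that mhGAP wording in the PCP's notes reveals the arm. No passage says that PCPs must write in mhGAP terms or that wording is scored, and Participants defines the disorders for both arms in general terms that pair the conventional label with the mhGAP-style one. That reading is speculative.

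Finally, the PHQ comparison is a partial check outside mhGAP, and the analysis is descriptive. Both soften the consequence, but the PHQ does not define correct diagnosis, and the pilot's rates still feed the next trial's sample size.

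**Conclusion.** The point holds in a limited form. The verified-diagnosis rate, a primary outcome, has no stated protection against anchoring on the PCP's diagnosis, and masking to arm does not supply it. Anchoring would overstate accuracy in both arms and understate a true difference: 20 points would read as 15 at a = 0.25 and 10 at a = 0.50, all on assumed rates. The shared yardstick may work the other way.

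A reader might infer that the design is biased in favour of the intervention, or try to attach a fixed artificial advantage to it. The document supports neither: it gives no rates, the two effects oppose each other, and their net direction is unknown. The change is worth making because it is cheap and improves a primary outcome, not because a bias of known size has been shown.

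**What to change.** **Intervention.** State that the psychiatrist records and signs a diagnosis, and whether referral is indicated, before seeing the PCP's diagnosis and management. These are then shown for the management rating and the safety check, so the existing safety provisions stay as they are. Data staff compute agreement from the two forms.

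**Allocation concealment.** Limit the masking claim to the PCP's allocation.

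**Primary outcomes and statistical analysis.** Report the outcome as concordance with mhGAP-based diagnosis. Agreement with a standard diagnostic classification may be added as a secondary measure.

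**Cost.** The visit and the psychiatrist are unchanged, with one added form, a slightly longer assessment and no effect on sample size. Because Trial status says that the study has commenced, apply the change to both arms from a recorded date and note that the two monitoring periods may not be fully comparable.

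**Limit.** Every patient sent is still known to be PCP-positive, and patients may disclose their diagnosis, so the change reduces anchoring without removing it.
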